## Methods

### Study design

The proposed study is designed as a prospective, multicenter, two-arm parallel group, single-blind RCT. Patients with plaque psoriasis will be randomly assigned to the treatment group (moving cupping) or the placebo group (sham moving cupping). Eligible participants will receive 4 weeks of treatment and a total of 8 weeks of follow-up (Table 1).

**Table 1 Tab1:** Study schedules of enrollment, intervention, and assessment

	Study period							
	Enrollment	Allocation	Treatment period				Follow-up period	
Time point	-week_1_	0	week_1_	week_2_	week_3_	week_4_	week_6_	week_8_
Enrollment								
Eligibility screen	**×**							
Informed consent	**×**							
List other procedures	**×**							
Allocation		**×**						
Interventions:								
Basic treatment plus moving cupping therapy								
Basic treatment plus moving cupping placebo								
Assessments:								
PASI	**×**	**×**	**×**	**×**	**×**	**×**	**×**	**×**
BSA	**×**	**×**	**×**	**×**	**×**	**×**	**×**	**×**
PGA	**×**	**×**	**×**	**×**	**×**	**×**	**×**	**×**
DLQI		**×**	**×**	**×**	**×**	**×**		
VAS		**×**	**×**	**×**	**×**	**×**	**×**	**×**
TCMSSS		**×**	**×**	**×**	**×**	**×**		
Vital signs	**×**	**×**	**×**	**×**	**×**	**×**		
Routine blood test	**×**					**×**		
Blood biochemical test	**×**					**×**		
Routine urine test	**×**					**×**		
Food allergen test	**×**							
Combined medications	**×**	**×**	**×**	**×**	**×**	**×**		
Pregnancy test	**×**							
Physical examination	**×**					**×**		
Adverse event		**×**	**×**	**×**	**×**	**×**		
Serious adverse events		**×**	**×**	**×**	**×**	**×**		

BSA, body surface area; DLQI, Dermatology Life Quality Index; PASI, Psoriasis Area and Severity Index; PGA, Physician’s Global Assessment; PR-QoL, patient-reported quality of life; TCMSSS, Traditional Chinese Medicine syndrome scoring scale; VAS, visual analog scale

### Patient and public involvement

Patients were involved in the design of the RCT.

### Recruitment

We plan to recruit 122 patients with plaque psoriasis for this study. They will be evenly distributed among six hospitals using fixed enrollment. Recruitment will occur at the Yueyang Hospital of Integrated Traditional Chinese and Western Medicine (Shanghai, China), Shaanxi Traditional Chinese Medicine Hospital (Shaanxi, China), First Affiliated Hospital of Heilongjiang University of Traditional Chinese Medicine (Heilongjiang, China), the Affiliated Hospital of Jiangxi University of Traditional Chinese Medicine (Jiangxi, China), Hospital of Traditional Chinese Medicine, Xinjiang Medicine University (Xinjiang, China), and Shijiazhuang Hospital of Traditional Chinese Medicine (Shijiazhuang, China). Eligible recipients will be recruited via social media, word of mouth, and dermatology outpatient clinics at local hospitals. Each hospital will designate three dermatologists for patient recruitment and one physician (dermatologists trained and qualified to perform moving cupping) for moving cupping treatment. Patients will be informed and asked to provide written informed consent prior to study commencement. Figure 1 presents a flowchart of participant enrollment and analysis throughout the course of the trial. Researchers will obtain recipient consent prior to trial participation. All potential and enrolled recipients’ personal information will be recorded, kept in a secure folder, and made accessible only to the researchers in order to protect their privacy.

**Fig. 1 Fig1:**
[figure not shown]
Consolidated Standards of Reporting Trials diagram of participant enrollment and analysis

### Participant screening

All patients who are diagnosed with plaque psoriasis will undergo laboratory blood testing before inclusion, including a complete blood cell count, liver function test, renal function test, and pregnancy test. Additionally, routine urine tests, vital sign monitoring, and physical examinations will be performed (Table 1).

### Criteria

The inclusion criteria are as follows: meet the 2018 China College of Dermatology diagnostic criteria for plaque psoriasis; skin lesions involve ≤ 10% BSA (the lesions are mainly located on the torso/limbs, palm/sole, or face/scalp, with the vulva area being unaffected); aged 18–65 years; provide consent to participate in the study and sign the informed consent form.

The exclusion criteria are as follows: any clinically active skin diseases other than moderate to severe psoriasis vulgaris that might confound or influence the study aim; patients who received any systemic treatments within 4 weeks before the baseline visit; patients who received topical treatment within 2 weeks before the baseline visit (e.g., corticosteroids, ultraviolet light therapy including sunbathing); patients with an active infectious disease that is difficult to control; patients with a history of severe systemic disease, an alanine aminotransferase or aspartate transaminase level greater than 1.5-fold that of the average; any of the main routine blood indices (white blood cell count, red blood cell count, hemoglobin level, platelet count) lower than the normal limit, or other laboratory abnormalities; immunocompromised patients who may experience skin allergies or infection with moving cupping therapy; pregnant or lactating women; patients with a history of alcohol or drug abuse; and patients with a history of serious mental illness.

The exit/termination criteria were as follows: patient lost to follow-up; violation of the research plan (including lack of compliance [medication, contraindication, interview plan]); adverse events (including worsening of psoriasis above baseline [for example, PASI > 125%]) [27]; and pregnancy.

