
Moving cupping therapy has been widely used for the treatment of plaque psoriasis, which is safe and associated with few adverse reactions, mainly local blisters. Additionally, it has been recognized by a large number of peers and patients. One study compared the efficacy of moving cupping and narrowband ultraviolet B based on oral Chinese herbs and found that moving cupping has clear advantages, but lacked high-quality medical evidence [26]. Therefore, we designed a multicenter, prospective, single-blind, placebo-controlled, RCT to evaluate the safety and efficacy of moving cupping therapy for plaque psoriasis.

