#### Moving cupping placebo

A special perforated cup made of the same material as that used for the intervention group will be selected and used during the same manipulation method as described for the intervention. Due to the perforated design, the fire cannot burn the air in the cup; therefore, it cannot form a negative pressure adsorption force. This simulates the form of moving cupping therapy without the therapeutic effects (Fig. 2).

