### Safety monitoring

All participants will be advised to remain under supervision in the clinical research unit for 15 minutes after treatment. In addition, data of the participants will be monitored by the research team to detect any adverse events throughout the study, such as skin damage or potential allergies. All potential adverse events will be recorded. If any participant experiences an adverse effect due to trial participation, they will receive free treatment and compensation accordingly. If any concerns of the participants are identified during screening or clinical assessment, further clinical evaluations and/or investigations will be performed immediately. If concerns are identified during the study, the participants will be withdrawn.

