### Sample size

The sample size of the current trial was calculated based on the following formula [33]:
$$ {\mathrm{n}}_1={\mathrm{n}}_2=\frac{p_1\times \left(1-{p}_1\right)+{p}_2\times \left(1-{p}_2\right)}{{\left({p}_2-{p}_1\right)}^2}\times {\left({\mu}_{\alpha /2}+{\mu}_{\beta}\right)}^2 $$

According to recently published clinical trial results [27], the PASI-50 reached 62.1% (P_1_) in the study group and 35.3% in the control group (P_2_). Therefore, we assumed that the inspection level (α) was 0.05 and the power was 0.8 (β = 1-power = 0.2). For the two-sided tests, 51 participants will be required for each group. Given a 20% loss to follow-up, we expect to require 61 participants for each group. Therefore, this trial will require at least 122 participants.

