### Missing data

The possibility of loss to follow-up has been considered and will be calculated as a part of the sample size estimation. The dropout rates and reason will be recorded. In addition, we will account for other types of randomly missing data by treating dropouts as non-success or non-survival using the intention-to-treat principle.

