### Ethics and dissemination

The study has been approved by the ethics committee of Yueyang Hospital of Integrated Traditional Chinese and Western Medicine (ref. approval no. 2019–003). Patients will be informed at the beginning of the study that they have the right to withdraw from the study at any time without providing a reason. Even in the event of a withdrawal, the required treatment will be provided to the patient. The results of the study will be published in an international peer-reviewed journal.

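### Exit for any adverse event or undefined concern, with dropouts scored as failures, may turn manageable local reactions to cupping into non-responders (minor; bias against cupping)

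*Protocol article*

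**What the plan says.** The exit and termination list under Criteria includes "adverse events (including worsening of psoriasis above baseline [for example, PASI > 125" per cent. Worsening of psoriasis is only an example within the category. No grade, seriousness, relatedness or manageability limit is attached to adverse events in general.

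Safety monitoring has the team watch participants "to detect any adverse events throughout the study, such as skin damage or potential allergies". It offers free treatment and compensation for adverse effects, and further evaluation of concerns found at screening or clinical assessment. It then ends: "If concerns are identified during the study, the participants will be withdrawn."

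Missing data provides for "treating dropouts as non-success or non-survival using the intention-to-treat principle". Primary parameters defines the primary outcome as the proportion with at least a 75% fall in PASI at week 4, so a dropout scored this way is a non-responder.

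On expected reactions, Background calls moving cupping "safe and associated with few adverse reactions, mainly local blisters". Of the perforated sham cup, Moving cupping placebo says "it cannot form a negative pressure adsorption force".

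**The concern.** Read literally and together, these sentences let a mild local reaction end participation and then count as a treatment failure. The main reaction named is a local blister. The sham has no suction, so such reactions should be more frequent in the active arm. A responder analysis would then mix two things: whether cupping cleared the psoriasis, and whether a patient had a skin reaction that could simply have been dressed and followed.

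Scoring patients who truly cannot continue as failures is a standard conservative choice and is not in question. The weak spot is narrower: nothing in the article separates a reaction that can be managed from one that must stop treatment. At stake are a diluted treatment difference, some power, and patients who could have completed the course.

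**Working it through.** **1. Text.** Three links are needed.

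- *Exit:* Criteria names adverse events without limit, and Safety monitoring makes withdrawal mandatory for concerns it does not define. A blister is not excluded by either, but neither names it.
- *Scoring:* Missing data scores dropouts as non-success. It does not say whether a mandated exit is a dropout, and no section says whether PASI is still taken after exit.
- *Imbalance:* that blisters fall mainly in the active arm is an inference from Background and Moving cupping placebo. The sham also uses flame, Vaseline and rubbing, so sham reactions and exits for worsening are possible.

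**2. The plan's own figure.** Inputs from Sample size: p1 = 0.621, p2 = 0.353 (PASI-50 rates), two-sided alpha 0.05, power 0.80.

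n = [p1(1−p1) + p2(1−p2)] / (p1−p2)² × (1.960 + 0.842)²
= (0.2354 + 0.2284) / 0.0718 × 7.849 = 50.7, so 51 per group, as stated.

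The allowance for loss gives 51 × 1.2 = 61.2, stated as 61.

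**3. Illustration of exits scored as failures.** The same formula solved for power at 61 per arm:

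Power = Φ( d / √{[p1′(1−p1′) + p2′(1−p2′)]/61} − 1.96 ), with d = p1′ − p2′.

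Assumptions: k exits in the active arm, unrelated to response, so p1′ = 0.621 × (1 − k/61); no other losses. Each exit lowers the expected difference by 0.621/61 = 0.0102, about 1.0 percentage point.

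| Active-only exits k | p1′ | Difference | Power |
|---|---|---|---|
| 0 | 0.621 | 26.8 points | 86.7% |
| 1 | 0.611 | 25.8 points | 83.9% |
| 2 | 0.601 | 24.8 points | 80.7% |
| 3 | 0.590 | 23.7 points | 77.2% |

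For k = 3: 0.237 / √[(0.2418 + 0.2284)/61] = 0.237/0.0878 = 2.70; 2.70 − 1.96 = 0.74; Φ(0.74) = 77%.

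**4. If the sham arm also loses patients.** With three active exits and sham exits at half that rate, p2′ = 0.353 × (1 − 1.5/61) = 0.344 and power is 80.3%. At an equal rate, p2′ = 0.353 × (1 − 3/61) = 0.336 and power is 83.1%. The loss therefore depends on the imbalance as well as on the number of exits.

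**5. Limits.** The protocol gives no blister rate and no exit rate, so every k is assumed. The rates are PASI-50, whereas the primary outcome is PASI-75. The loss per exit is the active response rate divided by 61, so at a lower PASI-75 rate each exit would cost less than 1 point. The 86.7% starting value exceeds 80% only because all 61 patients are used; the 20% allowance for loss supplies that headroom.

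**The case against.** The strongest reply is that this is a condensed article. A list of exit reasons need not mean that every adverse event compels exit, and the full protocol may grade events or leave them to the investigator's judgement. The one example given is marked worsening, which suggests substantial events. The intended treatment turns the skin purple, so a rule expelling anyone with visible skin change cannot be what was meant. Adverse effects have their own response, free treatment. The concerns sentence does not mention blisters. The non-success rule is introduced for other types of randomly missing data, and an exit forced by a treatment reaction is not random missingness. Background also calls reactions few.

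Most of this stands, and it limits the point. A reader might infer that blistered patients will in fact be removed and counted as failures, or that the trial will fall below its planned power. The documents support neither: they do not equate a blister with a concern, do not state that a mandated exit is a dropout, and give no rate from which a loss of power could be predicted.

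What does not fall away is the wording itself. The exit criterion is unqualified and the withdrawal sentence is mandatory. Nothing in the article exempts manageable reactions or provides for a PASI assessment after exit. These are rules as stated, not only details left out.

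**Conclusion.** The point holds as a minor one. The exit and withdrawal wording sets no threshold. If exits under it are handled as dropouts, a patient with an expected, manageable local reaction would be scored a non-responder, more often in the active arm than in the sham arm. The resulting bias is conservative: it can hide or shrink a real effect, but cannot produce a false finding in favour of cupping.

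Its size is unknown. On the assumed exits in the illustration, one or two active-only exits leave power above 80%, and the third takes it below. That result rests on PASI-50 planning rates, no other losses, and exits unrelated to response and confined to one arm. It shows the direction and scale of the mechanism and is not a forecast.

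**What to change.** Replace the bare adverse-event entry under Criteria and the last sentence of Safety monitoring with one rule for both arms, for example:

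> Expected local reactions such as blisters are recorded and managed without exit. Only serious adverse events, events that the investigator judges unsafe for continued cupping, or the defined PASI worsening stop treatment. Patients who stop treatment still have PASI assessed at week 4 if they agree.

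Keep the non-success rule in Missing data for patients with no week-4 PASI.

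The cost is small: wording in two places, slightly more adverse-event follow-up for patients who stay in, and a week-4 visit for those who stop. Reasons for dropout are already recorded, and Ethics and dissemination already states: "Even in the event of a withdrawal, the required treatment will be provided to the patient." Some contact after withdrawal is therefore already foreseen.

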### Randomization, allocation, and blinding

Once eligibility is confirmed and consent is obtained, participants will be block-randomized using a non-stratified, permuted block with varying lengths (*n* = 6 blocks; patient distribution = 1:1) for each arm/group. Independent statisticians will provide computer-generated random sequences. Distribution will be conducted by a central web-based interactive randomization service system. When a participant is eligible, the researcher who conducts the random grouping will need to log onto the website to view the grouping situation of the participant. Due to the nature of moving cupping, it is not possible to blind the operating physician involved in treatment application. To ensure blinding, we will use a placebo cup to simulate the treatment of moving cupping and shield the patient’s eyes with a black opaque eye mask. The treatment device will be of the same size and material as well, and the treatment method will maintain consistent frequency and intensity, but with no adsorption force. Each hospital will designate one operating physician who is a dermatologist trained to perform moving cupping therapy and has obtained the relevant operational qualifications. The operating physician will not participate in the statistical analysis, and the treatment plan and grouping will be known only by the statistical analyst.

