This study will be the first placebo-controlled study of moving cupping for the treatment of plaque psoriasis with multiple centers, double-arm parallel groups, and a single-blind RCT. Furthermore, the study has several advantages. The first is that it will use a placebo control to exclude the placebo effect, reduce the risk of bias, and define the clinical efficacy of moving cupping for the treatment of plaque psoriasis. The second advantage is that, because of the large land area of China, the study will include a total of six hospitals in different regions, thus including various ethnic and socioeconomic populations. As such, its experimental design will increase the generalizability of the trial outcomes. However, this study also has some limitations. Due to the particularity of moving cupping therapy, it is difficult for different operators to maintain the same strength when moving the cup. Furthermore, because different cup sizes will be selected for the different treatment sites, adsorption forces will be inconsistent. All of these limitations may lead to the risk of bias. The placebo cupping therapy method has been used previously in only two clinical trials [37, 38]. Although the moving cupping placebo lacks absorption during treatment, we found that most patients do not understand the specific operation of the treatment method; therefore, they cannot distinguish between the moving cupping placebo and moving cupping. Patients were blinded to whether they are accepting real or placebo cupping. In conclusion, this study aims to verify whether moving cupping therapy is effective for treating plaque psoriasis. We also hope to provide a safe and effective treatment for plaque psoriasis through this study.

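### Allocation is not stratified by hospital and no stated test adjusts for hospital, so likely chance imbalance within hospitals goes uncorrected and can cost precision and power

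*Protocol article*

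**What the plan says.** All places are in the protocol article.

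- **Randomization, allocation, and blinding:** participants are "block-randomized using a non-stratified, permuted block with varying lengths", with "patient distribution = 1:1". "Distribution will be conducted by a central web-based interactive randomization service system". The absence of stratification is stated outright.
- **Recruitment:** for the 122 patients, "They will be evenly distributed among six hospitals using fixed enrollment".
- **Randomization, allocation, and blinding:** "Each hospital will designate one operating physician who is a dermatologist trained to perform moving cupping therapy". Hospital and operator are therefore one factor.
- **Discussion:** "it is difficult for different operators to maintain the same strength when moving the cup", cup sizes and hence suction vary, and "All of these limitations may lead to the risk of bias". The same section presents the spread of hospitals over regions, ethnic groups and socioeconomic groups as a strength.
- **Primary parameters:** the primary outcome is binary, the proportion of patients with at least a 75% PASI reduction at week 4.
- **Statistical analysis:** qualitative variables get a chi-square or Fisher exact test, and repeated quantitative measures get general linear models. No hospital term or stratified test is named.

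**The concern.** The document expects hospitals to differ in operator, region and population. Each center also has its own designated researcher (Data collection and management), so PASI rating may differ by hospital too. Allocation makes no provision for any of this, and neither do the tests named. With some 20 patients per hospital, one central list balances the arms overall but not inside each hospital. If a hospital with a high response rate happens to hold more active than sham patients, part of the observed difference reflects the hospital. The unadjusted test also leaves between-hospital variation in the error. The trial is sized for 80% power, so lost precision is worth avoiding where that costs little.

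**Working it through.** **1. The plan's own figure.** The Sample size section uses 62.1% and 35.3%, two-sided alpha 0.05 and power 0.80:

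n = [0.621 × 0.379 + 0.353 × 0.647] / 0.268² × (1.960 + 0.842)² = 50.68, rounded up to 51 per arm. 51 × 1.2 = 61.2, taken as 61, so 122 in total. The figure reproduces, and its formula contains no hospital term.

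**2. Patients per hospital.** 122 / 6 = 20.3, so four hospitals of 20 and two of 21.

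**3. Imbalance within hospitals.** Simulated: random order of arrival and one central unstratified list, with blocks of 6 or of varying length 2/4/6, against separate hospital lists.

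| | One list, blocks of 6 | One list, blocks 2/4/6 | Hospital lists |
|---|---|---|---|
| Mean arm difference in a hospital of 20 | 3.2 | 3.3 | 0.4 |
| Some hospital differs by 6 or more (13:7 or worse) | 70% | 70% | 0% |
| Some hospital differs by 8 or more (14:6 or worse) | 36% | 36% | 0% |

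Hand check for one hospital of 20: drawing 20 from 61 active and 61 sham patients, the hypergeometric probability of 7 or fewer, or 13 or more, active patients is 0.22. The simulation gives 0.22 to 0.23. No run left a hospital with only one arm.

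The article says block lengths vary but attaches the number 6 to the blocks without saying what it counts. The table shows that this ambiguity does not affect the result.

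**4. Validity.** With no treatment effect and one unstratified list, the mean estimated difference is 0.00. The chi-square type I error is 4.9%, 5.0%, 4.9% and 5.5% at hospital standard deviations (SD, logit scale) of 0, 0.5, 1.0 and 1.5.

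**5. Size of one unlucky split.** Take a 14:6 split in a hospital whose response rate is 20 points higher (assumed). The shift in the risk difference is (14 − 6)/61 × 0.20 = 2.6 points. The assumed effect is 62.1 − 35.3 = 26.8 points.

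**6. Precision.** At SD 1.0 with no treatment effect, the standard error of the risk difference is 0.085 unstratified and 0.080 stratified. The added variation is √(0.0851² − 0.0802²) = 0.028, or 2.8 points.

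**7. Power.** All 122 analysed at the article's two rates. The hospital SD is an assumption, shown over a range. CMH is the Cochran-Mantel-Haenszel test by hospital.

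| Hospital SD (logit) | Unstratified list, chi-square | Unstratified list, CMH | Hospital lists, CMH |
|---|---|---|---|
| 0 | 86% | 84% | 85% |
| 0.5 | 83% | 81% | 83% |
| 1.0 | 72% | 77% | 78% |
| 1.5 | 59% | 69% | 70% |

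Read across the rows. Part of the fall down each column arises because a fixed odds ratio gives a smaller overall risk difference as hospitals spread out (0.27 at SD 0, 0.22 at SD 1.0). Repeat simulations put the CMH gain on the unstratified list at about 2 to 4 points at SD 1.0 and 7 to 10 at SD 1.5, with a loss of about 3 points at SD 0.

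**The case against.** A reader might infer that operator effects are confounded with treatment. The article does not support that. Every operator gives both real and sham cupping, no operator is tied to one arm, and allocation is random and central. Step 4 shows no average bias and no inflation of type I error. The 70% is the chance of an uneven split somewhere, not a measure of harm, and step 5 shows that the harm from one such split is small.

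A reader might also infer that the trial will ignore hospital in its analysis. The article does not say so. It is a condensed account, and a separate analysis plan may add a hospital term. What can be said is that allocation is expressly non-stratified and that the tests it names for a binary outcome are unadjusted.

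Two further objections stand. First, stratification would not remove the operator problem that the Discussion describes. For the sham, "the treatment method will maintain consistent frequency and intensity, but with no adsorption force", so differences in suction, and probably most of the effect of pushing strength, act in the active arm. That is variation of the treatment effect between hospitals, which neither stratified allocation nor a hospital main effect removes. Second, a single central list is defensible: with an unblinded operator, separate hospital lists make the next assignment easier to guess. The Timeline section also says that recruitment has begun.

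What the objections leave untouched is that a hospital-adjusted test is a better and cheap choice in a trial that itself expects its hospitals to differ.

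**Conclusion.** The point holds as one of efficiency, not validity. Chance imbalance within hospitals is likely (70% for some hospital at 13:7 or worse) and no stated analysis corrects for it. If hospitals are similar (SD 0 to 0.5), nothing is lost by leaving the test unadjusted. If they differ strongly (SD about 1.0 to 1.5), the unadjusted test gives up roughly 2 to 10 points of power compared with CMH on the same list. The article gives no between-hospital variation, so which case applies is unknown. The power levels also rest on the rates used for sizing, which are for a 50% PASI reduction, whereas the primary outcome is a 75% reduction. They therefore serve to compare methods, not to predict this trial's power.

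**What to change.** 1. Prespecify, before unblinding, a hospital-adjusted primary analysis: a Cochran-Mantel-Haenszel test stratified by hospital, or logistic regression with hospital as a covariate. If the analysis plan already does this, say so in the protocol.
2. Add a hospital term to the general linear models for the quantitative outcomes.
3. Report the treatment effect by hospital as a descriptive check of consistency. This is the part that addresses operator and suction differences; about 10 patients per arm in each hospital is too few for a firm interaction test.
4. State what the number 6 in the block description means. If it means one list per hospital, the word non-stratified is wrong.
5. Stratify the web randomisation by hospital, with varying block sizes, only if enrolment has not progressed. Otherwise leave the list unchanged; the adjusted test recovers most of the power (77% against 78% at SD 1.0).

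The cost is a few lines of analysis text and about 1 to 3 points of power if hospitals turn out to be alike. The sample size stays at 122.
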